#### Outcomes {12}

Primary outcome:28-day mortality [time frame: 28 days]All-cause mortality of participants will be monitored for 28 days to assess the safety and efficacy of C-IVIG

Secondary outcomes:Immediate (within 24 h) or serious adverse events (throughout the hospital stay) [time frame: 28 days]Clinical status according to 7 category ordinal Scale [time frame: 28 days (till hospital stay)Not hospitalized and no limitations of activitiesNot hospitalized, with limitation of activities, home oxygen requirement, or bothHospitalized, not requiring supplemental oxygenHospitalized, requiring any supplemental oxygenHospitalized, requiring noninvasive ventilation or use of high-flow oxygen devicesHospitalized, receiving invasive mechanical ventilationDeathChange in Horowitz index (PaO_2_/FiO_2_ ratio use to assess lung function) during hospital stay [time frame: 28 days]Change in C-reactive protein (CRP) levels, radiological findings, IL-6 level, and anti-SARS-CoV-2 antibody levels [time frame: 5 days]

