#### Sample size {14}

Three hundred nine participants will be enrolled in the study. Sample size was determined by taking proportion of survival in intervention group (P1) = 75%, proportion of survival in control group (P2) = 40%, power of test (1-β) = 90%, with the sample ratio 2:1 (test to control), superiority margin 0.15, and drop rate 30%. The calculated total sample size is 309 patients, 206 tests and 103 control. The calculated sample size was determined with the help of online sample size calculator (www.riskcalc.org) taking 99% confidence level (11).

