### Statistical methods

#### Statistical methods for primary and secondary outcomes {20a}

Patients will be randomized at a ratio of 2:1 to receive either C-IVIG with standard of care or standard of care only. The data to be analyzed will be blinded using the SPSS software 24.0. All randomized study participants will be included in the intention-to-treat population and all participants completing the study period will be analyzed (complete case analysis). Normality of continuous data will be checked by the Shapiro-Wilk test, and parametric or non-parametric tests will be applied accordingly. Continuous variables will be presented as mean (± SD) or median (interquartile range), and categorical variables will be presented as percentages. In the primary analysis strategy, we will use the Kaplan–Meier curve (Breslow test) that compares the time to reach the primary end point in the trial groups. Hypothesis testing of outcomes for the assessment of safety and efficacy parameters will be conducted by Mann-Whitney *U* test or independent *t*-test. Categorical data will be compared with chi-square test, and value of the two-sided Fisher exact test will be recorded. An estimate of the relative risk and 95% confidence interval will also be reported. Hypothesis testing will be conducted at a significance level of 0.05.

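### The Horowitz-index outcome has no place for death; the stated complete-case rule, applied to it, would compare survivors selected by an outcome the drug is expected to change

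*Protocol article*

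**What the plan says.** Outcomes {12} lists the change in Horowitz index third among the secondary outcomes. It is the change in PaO2/FiO2 "ratio use to assess lung function) during hospital stay [time frame: 28 days". The text of that section gives no assessment day for the index and no rule for a patient who dies.

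Its neighbours are treated differently. "Clinical status according to 7 category ordinal Scale" has death as its worst category, and CRP, IL-6, radiology and antibody levels have a 5-day time frame.

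Statistical methods {20a} defines an intention-to-treat population, then says that "all participants completing the study period will be analyzed (complete case analysis". Continuous outcomes are compared by t-test or Mann-Whitney test. The missing-data section {20c} leaves the choice open between multiple imputation and complete cases, and does not mention death.

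Sample size {14} assumes "proportion of survival in intervention group (P1) = 75%, proportion of survival in control group (P2) = 40" per cent, that is, 25% and 60% deaths.

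**The concern.** In severe COVID-19 the patients with the worst lungs are likely to be among those who die, and after death there is no index to measure. Under the plan's own assumptions this removes 60% of controls but only 25% of C-IVIG patients. If only those who complete the study period contribute, the control survivors are the more strongly selected group, and randomisation no longer protects the comparison.

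The direction is awkward. Each patient whom C-IVIG keeps alive, and who would have died on control, enters the C-IVIG arm only. If such patients recover lung function less well than the others, they pull that arm's average down. The lung result could then look weaker than the drug's true effect, or point the other way, beside a favourable mortality result.

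**Working it through.** **Inputs from the protocol article.** Survival 75% on C-IVIG and 40% on control, arms of 206 and 103 ({14}); completers analysed by t-test or Mann-Whitney, significance level 0.05 ({20a}).

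**Inputs not in the documents (assumed).** The correlation ρ between a patient's latent prognosis and the change in index, ranged from 0 to 0.8; and, for figures in mmHg, an SD of 80 mmHg for the change.

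**The plan's own figure.** Superiority by a margin with unpooled variance, one-sided 0.05, power 90%, 2:1:
- control n = (1.6449 + 1.2816)² × (0.40×0.60 + 0.75×0.25/2) / (0.75 − 0.40 − 0.15)² = 8.5639 × 0.33375 / 0.04 = 71.45, rounded up to 72;
- with 30% dropout, 72/0.70 = 102.9, rounded up to 103; 103 + 206 = 309.

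This matches the stated total. It does not match the stated 99% level, which gives 468 one-sided or 537 two-sided. That is a separate matter; the stated arm sizes are used below.

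**Step 1: who survives.** Control: 0.40 × 103 = 41.2. C-IVIG: 0.75 × 206 = 154.5. If everyone who would survive on control also survives on C-IVIG, then (0.75 − 0.40)/0.75 = 46.7% of C-IVIG survivors would have died on control.

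**Step 2: bias without a distributional model.** If the change in those extra survivors is G mmHg worse than in the others, the survivor difference equals the true effect minus 0.467 × G. For G = 25, 50 and 100 the bias is −11.7, −23.3 and −46.7 mmHg.

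**Step 3: bias with a normal latent prognosis.** Let patients above a threshold survive. The mean latent value of the top fraction p is φ(z)/p, with z the threshold.
- Control, p = 0.40: 0.3863/0.40 = 0.966.
- C-IVIG, p = 0.75: 0.3178/0.75 = 0.424.
- Gap: 0.542 SD. The bias is −0.542 × ρ, in SDs of the change among all patients.

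| ρ | Bias if C-IVIG changes no one's index (SD) |
|---|---|
| 0 | 0 |
| 0.4 | −0.22 |
| 0.6 | −0.33 |
| 0.8 | −0.43 |

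If C-IVIG instead improves the latent prognosis itself, the shift that moves survival from 40% to 75% is 0.2533 + 0.6745 = 0.928 SD. Survivors then show 0.928 − 0.542 = 0.386 SD, about 42% of it. In the index this is a true 0.37 to 0.74 SD seen as 0.15 to 0.31 SD for ρ = 0.4 to 0.8.

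**Step 4: what a trial of this size would show.** 3,000 simulated trials per case, 206 v 103, survivors only, SD 80 mmHg, Mann-Whitney at two-sided 0.05:

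| ρ | No lung effect: mean difference | Significant apparent harm | True +20 mmHg: mean difference | Significant apparent harm |
|---|---|---|---|---|
| 0 | about 0 | 3% | +20 | 0% |
| 0.3 | −13 | 15% | +7 | 1% |
| 0.5 | −22 | 37% | −2 | 3% |
| 0.7 | −30 | 72% | −10 | 14% |

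**Step 5: the alternatives.** If those who die contribute an unselected last in-hospital value and there is no lung effect, the bias disappears: the probability that a C-IVIG patient does better than a control is 0.50, and apparent harm occurs in 2% to 3% of trials. If all planned deaths are ranked worst, again with no lung effect, that probability is 0.64 to 0.68 for ρ from 0 to 0.7 (at ρ = 0: 0.75×0.60 + 0.5×0.75×0.40 + 0.5×0.25×0.60 = 0.675). The test then favours C-IVIG significantly in 98% to 100% of trials and never shows harm. At 28-day mortality, that analysis mostly restates mortality.

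**The case against.** A reader might infer that the plan fixes a survivor-only analysis. It does not. The completers sentence also governs the primary outcome, where dropping the dead would leave no deaths to analyse, so a death within 28 days may count as completion. A change over the hospital stay can be computed from values taken before death, and nothing shown discards them. The retention section {18b} keeps data collected before loss to follow-up, and {20c} allows multiple imputation. This stands: survivor-only is one reading. The others are not clear repairs, however. Imputation would invent lung function after death. A last value ends at death for some and at discharge for others, and the Discussion reports earlier discharge of severe patients in the previous trial, so observation length may differ by arm. The readings can give different answers from the same data.

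A reader might also infer that no assessment day exists. Table 1 is not shown and may set one.

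A third tempting inference is that the trial would make a life-saving drug look harmful to the lungs. That needs a substantial link between prognosis and the index. At ρ = 0 there is no bias, and cancelling a true +20 mmHg takes a correlation of about 0.5 under the assumed SD.

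Nor is the index the main efficacy measure. The protocol gives it no such label, and the efficacy measures named for the interim analyses are mortality and clinical status. Detail on death in a secondary outcome could be left to an analysis plan, but here a stated analysis rule, applied as written, leads to the selected comparison.

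**Conclusion.** The point holds as a conditional one. The outcome gives no place to death, and the complete-case rule in {20a}, applied to it under the planned 60% v 25% mortality, would compare about 41 control survivors with about 154 C-IVIG survivors, which is not a randomised comparison. The bias against C-IVIG runs from 0 to about 0.43 SD for an assumed correlation of 0 to 0.8.

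That size rests on the planned 28-day mortality, on a single normal prognosis deciding death, and on a correlation that the documents do not give. At an earlier day fewer patients have died and the bias is smaller, provided that early deaths form a similar share of all deaths in both arms. The outcome is secondary; 28-day mortality and the ordinal scale are untouched by this mechanism. It should be settled before analysis, but it does not threaten the trial's main conclusion.

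**What to change.** In {12} and {20a}, state that:
- the change in Horowitz index is analysed in all randomised patients from baseline to one common early day (for example day 5, already the time frame for CRP and IL-6; if Table 1 sets a day, keep that one);
- deaths before that day are ranked worst, and the arms are compared by a rank test;
- a stated rule covers patients discharged before that day;
- any survivor-only comparison is descriptive.

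This takes about one sentence in each section. The result becomes a rank comparison instead of a mean difference in mmHg, and it partly reflects mortality, so it should be reported as a composite of death and lung function. An early day limits that overlap, because only deaths before it are ranked worst.

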#### Participant timeline {13}

The timeline of enrollment and intervention is given in Table 1.

**Table 1 Tab1:**
[figure not shown]
Time schedule of enrolment, interventions, assessments, and visits for participants

#### Sample size {14}

Three hundred nine participants will be enrolled in the study. Sample size was determined by taking proportion of survival in intervention group (P1) = 75%, proportion of survival in control group (P2) = 40%, power of test (1-β) = 90%, with the sample ratio 2:1 (test to control), superiority margin 0.15, and drop rate 30%. The calculated total sample size is 309 patients, 206 tests and 103 control. The calculated sample size was determined with the help of online sample size calculator (www.riskcalc.org) taking 99% confidence level (11).

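### The trial is sized to show a survival gain above a 0.15 margin, but the primary analysis is a Breslow test of no difference and no stated analysis uses the margin, so the stated 90% power describes a test that will not be run

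*Protocol article*

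**What the plan says.** Protocol article, Sample size {14}: the inputs are "proportion of survival in intervention group (P1) = 75" per cent, "proportion of survival in control group (P2) = 40" per cent, "power of test (1-β) = 90" per cent, a 2:1 allocation, and "superiority margin 0.15, and drop rate 30" per cent. The total is 309 (206 C-IVIG, 103 control), calculated "taking 99% confidence level".

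Outcomes {12}: the primary outcome is 28-day mortality. "All-cause mortality of participants will be monitored for 28 days to assess the safety and efficacy of C-IVIG".

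Statistical methods for primary and secondary outcomes {20a}: for the primary analysis, "we will use the Kaplan–Meier curve (Breslow test) that compares the time to reach the primary end point in the trial groups". The section also lists chi-square and two-sided Fisher tests for categorical data and a relative risk with a 95% confidence interval, and sets the significance level at 0.05. The margin appears nowhere outside the sample size section.

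**The concern.** Two hypotheses are in play. The sizing hypothesis is that survival on C-IVIG exceeds control by more than 15 percentage points. The hypothesis of the primary test is that the two survival curves are identical. Rejecting the second does not establish the first, and the power calculated for the first is not the power of the second.

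The choice of test adds a further difference. Breslow's test (generalised Wilcoxon) weights each death by the number still at risk, so early deaths count most. The stated outcome is whether a patient is dead by day 28, not on which day. A treatment that moves deaths later within the 28 days without preventing any could yield a significant primary result. At stake is what a significant result of a phase II/III mortality trial may be said to show.

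**Working it through.** **1. Reproduce 309.** Inputs from Sample size {14}: P1 = 0.75, P2 = 0.40, margin 0.15, power 0.90, ratio 2:1, dropout 30%. Superiority by a margin, unpooled variance:

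n(control) = [P2(1−P2) + P1(1−P1)/2] × (z_α + z_0.90)² / (P1 − P2 − 0.15)²

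The bracket is 0.24 + 0.09375 = 0.33375 and the denominator is 0.20² = 0.04. At one-sided 0.05, (1.645 + 1.282)² = 8.564, so n = 0.33375 × 8.564 / 0.04 = 71.45, rounded up to 72. Then 72/0.70 = 102.9, so 103 controls, 206 on C-IVIG, total 309.

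| Level | Controls before dropout | Total after dropout |
|---|---|---|
| one-sided 0.05 | 72 | 309 |
| two-sided 0.05 | 88 | 378 |
| one-sided 0.01 | 109 | 468 |
| two-sided 0.01 | 125 | 537 |

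Without the margin, the totals at one- or two-sided 0.05 or 0.01, with or without continuity correction, run from 105 to 198. So the margin did drive the sample size, and the stated 99% level did not.

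**2. Power of the margin test at 144/72 evaluable** (206 and 103 less 30%). SE = √(0.24/72 + 0.1875/144) = 0.0681, and 0.20/0.0681 = 2.938. Power = Φ(2.938 − z):

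- one-sided 0.05: Φ(2.938 − 1.645) = 90.2%
- two-sided 0.05: Φ(2.938 − 1.960) = 83.6%
- one-sided 0.01: Φ(2.938 − 2.326) = 72.9%
- two-sided 0.01: Φ(2.938 − 2.576) = 64.1%

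**3. Power against zero at 144/72.** For 75% v 40%, 0.35/0.0681 = 5.14, and Φ(5.14 − 1.96) is above 99.9%. Solving Φ(d/SE − 1.96) = 0.90 for the gain d gives 22.8, 21.5 and 17.9 points at control survival 40%, 60% and 75%.

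**4. A true gain exactly at the margin (55% v 40%).** A two-sided 0.05 test against zero rejects with probability Φ(0.15/√(0.55×0.45/n_t + 0.24/n_c) − 1.96). This is Φ(2.110 − 1.96) = 56% at 144/72 and Φ(2.524 − 1.96) = 71% at 206/103. Simulated under exponential survival at 206/103, Breslow rejects in 74% and the one-sided 0.05 margin test in about 6%.

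**5. Breslow with equal 28-day mortality.** The documents give no timing of deaths, so these are assumptions: true mortality 40% in both arms, 206/103, deaths uniform over the stated days, 3,000 simulated trials per row, two-sided 0.05.

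| C-IVIG deaths, days | Control deaths, days | Breslow | Log-rank | 28-day proportions |
|---|---|---|---|---|
| 1–28 | 1–28 | 5% | 5% | 5% |
| 4–28 | 1–28 | 6% | 5% | 4% |
| 3–28 | 1–26 | 8% | 7% | 6% |
| 4–21 | 1–14 | 31% | 14% | 5% |
| 8–27 | 1–14 | 59% | 23% | 5% |

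The Breslow rate depends on how far deaths are delayed. The comparison of 28-day proportions stays near 5% throughout.

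**The case against.** A Kaplan–Meier comparison with a Breslow test is a recognised way to analyse death over 28 days, and it is prespecified. The protocol calls itself a superiority trial and nowhere says that its report will claim a gain above 0.15. Twenty-eight-day death is categorical, so the chi-square or Fisher test and the relative risk in {20a} would probably be reported too, and would partly expose a treatment that only postpones deaths. All of this stands, and it limits the point.

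Three stronger readings are tempting, and the documents do not support them.

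- A reader might take the 56–71% rejection rate at 55% v 40% survival as a false-positive rate. Treatment truly helps there, so rejecting no difference is correct. It is an error only if a gain above 0.15 is then claimed.
- A reader might infer that Breslow generally inflates error here. The 30–60% figures need control deaths to end by day 14 while C-IVIG deaths run on to day 21 or 27. With the same timing the test holds 5%, and with mild delays it stays close to that.
- A reader might infer that the trial is underpowered. It is not under its own assumptions: for 75% v 40% the test against zero has more than 99% power, and 129 patients would suffice at two-sided 0.05 (30 controls, 43 after dropout, times three).

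What the objection does not remove is the contradiction itself. The article states both the margin and the primary test, so a separate analysis plan could reconcile them only by departing from one.

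**Conclusion.** The mismatch holds. The sample size rests on a 0.15 margin that no stated analysis tests, at a level (one-sided 0.05) that is not the 99% stated. The 90% power is thus not the power of the planned primary test, and a significant result would show that the survival curves differ, not that survival improved by more than 15 points. This conclusion needs no assumption beyond the standard unpooled formula, which returns 309 exactly.

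The Breslow weighting is a secondary and conditional part. It can produce significance with equal 28-day mortality, but the size runs from about 5–6% to 30–60% at 40% mortality and rests wholly on assumed death timing.

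**What to change.** Preferred: make the primary analysis the difference in 28-day mortality between randomised arms, stratified by site (randomisation already is), with a 95% CI and a two-sided 0.05 test against zero. Keep Kaplan–Meier with a log-rank test as support. Delete the margin and the 99% level from Sample size {14}. Restate power at 144/72 evaluable: above 99% for 75% v 40%, and 90% for a gain of about 23, 21.5 or 18 points at control survival 40%, 60% or 75%. The cost is rewording two sections, with no extra data. The downside is that the claim becomes superiority over zero, not over 0.15.

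If the margin is kept: state that success requires the lower confidence limit of the 28-day survival difference to exceed 0.15, name the level, and restate the power at 144/72. That is 90% with one-sided 0.05 (a 90% CI), 84% with a two-sided 95% CI, and 73% or 64% at one- or two-sided 0.01. Rewording alone then suffices only at one-sided 0.05. Holding 90% power at the other levels needs 378, 468 or 537 patients.

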### Trial design {8}

This is an adaptive, phase II/III, multi-center, randomized controlled, single-blinded superiority trial with parallel group design to assess the safety and efficacy of single dose of C-IVIG in patients with symptoms of severe COVID-19. Eligible participants will be randomly assigned in 2:1 ratio (206 tests: 103 controls) by block randomization method to receive C-IVIG plus standard of care (intervention group) or only standard of care (control group). The adaptive study design refers to adapting the strategy of trial based on interim analysis at three particular time points [12]. Outcome of the interim analysis will lead to making decision for terminating trial in case of serious adverse events or selecting a higher C-IVIG dose regime in case selected dose of C-IVIG (0.15g/Kg) not found efficacious. A flow chart of the trial design is shown in Fig. 1.

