#### Interim analyses {21b}

An interim analysis will be performed after recruitment of 15%, 30%, and 60% participants in the trial. It will assess primary outcomes of the study particularly focusing on the safety and efficacy of the infused drug. Safety of the intervention will be monitored in terms of any immediate or serious adverse event that can be observed after the administration of the drug. The efficacy of the intervention will be noted in terms of the patient's improvement in clinical status as compared to the control group.

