## Discussion

This phase II/III clinical trial is an adaptive, randomized controlled, multi-center, single-blinded superiority trial of SARS-CoV-2 specific polyclonal IVIG (C-IVIG) versus standard of care for patients hospitalized with severe COVID-19. Single dose of C-IVIG in combination with the standard of care was found to be both safe and efficacious in our previous clinical trial phase I/II while increasing the survival rate and reducing the risk of disease progression [13]. There were no significant changes observed when different doses of C-IVIG were compared in the phase I/II; however, it was found that C-IVIG dosage of 0.15 g/kg have significantly improved the therapeutic response in severe COVID-19 patients. These results warrant the phase II/III clinical trial study of C-IVIG, in order to evaluate its safety and efficacy in large sample size by comparing outcomes (28-mortality, hospital stay and drug-related adverse events) of C-IVIG along with SOC in intervention group and SOC only in comparator group provided during the hospital stay.

Study participant selection for this study is based on the results of our previous clinical trial where severe patients had 100% survivability and early hospital discharge than critical patients and comparator group. We evaluated that hospital stay, reliance on mechanical ventilation, and burden on hospital could be reduced if C-IVIG is administered to the severe COVID-19 patients by delaying the disease progression.

This is an adaptive clinical trial to investigate the risk-benefit analysis of C-IVIG administration for severe COVID-19 at first and second interim of the study. Major outcome variables to be assessed for interim analysis are adverse events, 28-day mortality, and change in clinical status of the patients. Fate of this clinical trial is based on whether the C-IVIG is safe and efficacious. If the treatment modality is found to be safe but not efficacious as compare to comparator group, we might select different dosage of C-IVIG for further study participants; if interim analysis indicate association of serious adverse events with administration of C-IVIG or with significant high mortality ratio in intervention group than comparator group or if incidence rate of COVID-19 is low till the study completion date, then this clinical trial would be early terminated due to aforementioned reasons.

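### The stated 90% power holds only for an unchanged dose, at one-sided 5% against the 0.15 margin; on that basis a replacement dose has about 58% to 86% against concurrent controls

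*Protocol article*

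**What the plan says.** The Sample size section {14} assumes 75% survival on C-IVIG and 40% on control, 90% power, 2:1 allocation, a superiority margin of 0.15 and 30% dropout. It says a 99% confidence level was used. The result is one pair of group sizes: "The calculated total sample size is 309 patients, 206 tests and 103 control".

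The dose is open to change during the trial. Trial design {8} provides for "selecting a higher C-IVIG dose regime in case selected dose of C-IVIG (0.15g/Kg) not found efficacious", and the section on modifying allocated interventions {11b} repeats this. The Discussion places the change inside this trial: "we might select different dosage of C-IVIG for further study participants". The timing is in Interim analyses {21b}: "An interim analysis will be performed after recruitment of 15%, 30%, and 60% participants in the trial". The Discussion, however, mentions only the first and second interim when it describes the adaptive risk-benefit assessment.

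Statistical methods {20a} lists a Kaplan–Meier comparison with the Breslow test, chi-square, two-sided Fisher exact and a relative risk with 95% confidence interval, at a significance level of 0.05. None of these is given a margin.

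**The concern.** The power calculation treats all 206 intervention patients as receiving one regimen. If the dose changes at an interim look, only patients recruited afterwards receive the new one, and only part of the control group is randomised alongside them. The trial is described as adaptive from the outset, so this is a path that the design provides for. A reader who sees 90% and 309 could take the figure to cover whichever dose the trial ends up testing.

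At stake is how a result for a replacement dose is read, and whether those deciding on a change know how much information is left. The answer depends on the hypothesis tested, and the sample size and analysis sections do not agree on that.

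**Working it through.** **Inputs.** From Sample size {14}: survival 0.75 v 0.40, margin 0.15, power 90%, 2:1, dropout 30%, total 309 (206 v 103). From Interim analyses {21b}: looks at recruited fractions f = 0.15, 0.30 and 0.60. Assumptions: the total stays at 309, and the new dose also reaches 75% survival.

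**Reproducing 309.** Superiority by a margin, unpooled variance:

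n(control) = [0.40×0.60 + 0.75×0.25/2] × (z_alpha + z_power)² / (0.35 − 0.15)²

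At one-sided 5%: 0.33375 × (1.645 + 1.282)² / 0.04 = 71.45, so 72 v 144 evaluable. Dividing by 0.70 and rounding up gives 103 v 206 = 309, exactly. Other levels do not give it:
- two-sided 5%: 126 + 252 = 378
- one-sided 1%: 156 + 312 = 468
- two-sided 1%: 179 + 358 = 537

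**Power with no dose change.** Power = Φ[(0.35 − margin)/SE − z_alpha], with SE = √(0.1875/n1 + 0.24/n2). With 144.2 v 72.1 evaluable, SE = 0.0680 and 0.20/SE = 2.94.
- one-sided 5%: Φ(2.94 − 1.645) = 90.2%
- one-sided 1%: Φ(2.94 − 2.326) = 73.0%
- two-sided 1%: Φ(2.94 − 2.576) = 64.2%

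So the 90% does not go with the 99% level stated beside it.

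**Power after a change.** Patients still to be recruited number 206(1 − f) and 103(1 − f), and 70% of them are evaluable. Margin 0.15, one-sided 5%:

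| Change at | Enrolled after, C-IVIG v control | Evaluable | 0.20/SE | Power v concurrent controls | Power v all controls (72.1 evaluable) |
|---|---|---|---|---|---|
| 15% | 175 v 88 | 123 v 61 | 2.71 | 85.7% | 89.0% |
| 30% | 144 v 72 | 101 v 50 | 2.46 | 79.2% | 87.1% |
| 60% | 82 v 41 | 58 v 29 | 1.86 | 58.5% | 79.4% |

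With the margin kept and a two-sided 5% level, power against concurrent controls is 77.3%, 69.1% and 46.0%.

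**Same patients, no margin, two-sided 5%**, closer to the tests listed in {20a}:

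| Change at | 0.35/SE | Normal approximation | Two-sided Fisher exact |
|---|---|---|---|
| 15% | 4.74 | 99.7% | 99.5% |
| 30% | 4.30 | 99.0% | 98.5% |
| 60% | 3.25 | 90.2% | 86.8% |

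The shortfall is therefore against the margin-based hypothesis to which the 90% refers. It largely disappears for a plain comparison of the new dose with concurrent controls.

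**The case against.** The strongest reply is that the analysis section specifies no margin test. On its tests a replacement dose that works as assumed keeps 87% power or more against concurrent controls, even after the 60% look. A reader might infer from the 58% that a non-significant result would be likely after a late change. The documents do not support that: on those tests the chance is about 10% to 13%, and even on the margin basis it is about 42% (100 − 58). This part of the reply stands. It does not rescue the 90% itself, because without the margin 206 v 103 has about 99.9% power at two-sided 5%, so the stated figure does not describe that test either. The reassurance also assumes that the new dose is analysed separately. Suppose instead that all randomised C-IVIG patients are pooled after a change at 60% and, as an illustration, the first dose had control-level survival. Pooled survival is then 0.6×0.40 + 0.4×0.75 = 0.54, and a plain two-sided 5% test has Φ(0.14/0.0711 − 1.96), or about 50%.

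A second reply is that the article nowhere promises 90% for a replacement dose and nowhere rules out a larger total. Both are correct. That 309 is kept is inferred from its being the only total given, and protocol amendments are possible.

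Third, the Discussion names only the first and second interim. If the third look cannot change the dose, the margin-based range is 79% to 86%.

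Finally, analysis detail after an adaptation can be left to the full protocol or the SAP. That is fair for the choice of controls or a re-estimation rule, but the point here is the scope and basis of a figure that this article states.

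**Conclusion.** The point holds in a limited form. The 90% applies to the design in which the dose is not changed, and only at one-sided 5% against the 0.15 margin. At the 99% level that the Sample size section states, it is 73% or 64% with no change at all. If the dose is changed, 309 is kept and the new dose reaches 75% survival, power on the one-sided 5% margin basis is about 86%, 79% and 58% against concurrent controls, or about 89%, 87% and 79% against all controls. The last figure in each set requires that the third look can change the dose.

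This does not show that the trial would be badly underpowered for a replacement dose on the tests it lists. Nor does it justify a rule that a dose introduced late be reported only as an estimate; that would be a preference, and it would downgrade a comparison with 87% to 90% power on the listed tests. No view is taken on which dose or dose-change rule is right.

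**What to change.** In Sample size {14}:

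- State that the 90% refers to the design with the dose unchanged.
- Reconcile the alpha and the margin with Statistical methods {20a}: say whether the hypothesis carries the 0.15 margin, and replace the mismatch between 99%, 0.05 and the one-sided 5% that yields 309 with one stated level and sidedness.
- Give the power for a new dose against concurrently randomised controls after a change at each look, with its assumptions (alpha, margin, dropout, survival on the new dose, total kept at 309). On the one-sided 5% margin basis these are about 86%, 79% and 58%. Without a margin at two-sided 5% they are 99.7%, 99.0% and 90.2% (Fisher exact 99.5%, 98.5% and 86.8%).
- Reconcile the three looks in {8} and {21b} with the two named in the Discussion, so that it is clear whether the 60% figure applies.

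The cost is wording and, on the margin basis, a less favourable power figure for the changed-dose path. Restating the power in this way needs no extra patients.
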